***Food intakes using 24-h recall***

A single day non-quantified 24-h recall of OVC will be obtained from the participants via their caregivers/families. The recall will cover all days in a week. The individual dietary diversity score (IDDS) of the OVC will be used to measure the nutritional quality of the reported intake of the OVC [30–32]. The IDDS is a simple count of food groups that an individual has consumed over the previous 24 h. When the participants’ recall is complete, the foods will be classified according to the Food and Agriculture Organization of the United Nations (FAO) food groups and scored on a scale of Yes (1) or No (0) [31]. If a food item from the group is consumed, it will score ‘1’ and if not it will score ‘0’. The nine food groups will be (i) cereals, roots and tubers (ii) dark green leafy vegetables (iii) other vitamin A rich fruits and vegetables (iv) other fruits and vegetables (v) legumes and nuts (vi) meat and fish products (vii) organ meat (viii) milk and milk products (ix) eggs. The IDDS is sensitive to assessing the change in diet before and after an intervention to detect any improvement [31].

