### Recruitment and retention of participants

Recruitment of participants will start during the start of the second term. We estimated that a total of 520 students aged (12–17 years) will be selected. Participants will be chosen from secondary schools in Soweto. The OVC will be followed up at their various orphanages or through their caregivers.

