#### (*a) Dietary intake assessments*

***Food intakes using photovoice***

The method of data collection here will be emancipatory participatory approach using photovoice and photo-assisted focus group discussions. Photovoice is a qualitative research method that enables participants to be involved in data collection by representing their experience, perception, concepts, and voices using photographs [21, 22]. The photographs will be used to capture participants’ viewpoints in the form of storytelling. It will enable participants of thisresearch to contextualise the photographs and have shared multiple viewpoints by explaining what the photographs mean to them during assisted group discussions [22–24]. A disposable camera with limited number of films will be provided to the caregivers/families of the OVC to take pictures of foods and environment where foods are provided to the OVC [25]. Participants will be trained in the use of the disposable camera. The caregivers/families OVC will be required to take pictures of food intakes OVC for three days, one of which must be weekend (Training will be provided). Such caregivers/families of OVC will be engaged in photo-assisted focus group discussions that is, they will be expected to explain what the pictures mean to them.

It will be clearly stated to the participants that, there will be no pictures of people but pictures of foods and environment only. The pictures will be used to initiate dialogue on the food intakes and food security of the OVC. The cameras will be recycled immediately the appropriate pictures have been selected. The length of the interview is estimated to be 35 min with another 25 min for discussion on the pictures taken. The group discussions will engage participants in reflective perspective analysis on the healthiness of the foods in which the photograph is taken during the three-day period.

The needs that will be identified in the food intakes of the OVC will be incorporated into the NEP that will be developed and implemented to capacitate the caregivers/families of OVC.

The photovoice will be followed with photo-assisted focus group discussions.

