### Intervention

The intervention will entail the implementation of the NEP at the orphanage homes. Selected constructs of the SCT and HBM will be incorporated to enhance learning, and positive changes in attitudes and dietary behavior to improve QoL, dietary diversity, physical activities, anthropometric status and academic performance of the OVC. The NEP will address the importance of nutrition in improving QoL and the secondary outcomes, and provide guidance on how to overcome the barriers to healthy eating to enable the caregivers of the intervention group to adopt typical behaviors [49, 51].

The intervention participants will receive nutrition education materials and the 12-week NEP. The NEP is proposed to consist of:(i)a NE trainer’s manual(ii)a participant’s workbook to be used at home by the intervention participants to revise the topics that will be taught. This proposal is expected to enhance participants’ confidence in performing acquired knowledge and skills [49, 51].(iii)flipcharts for pictorial demonstration; so that participants will compile evidence through visual literacy.(iv)a leaflet summarising the NEP for self-learning.

An attendance register will be kept for follow up and measure of attrition rates.

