## Sustainability aspects of this study

The involvement of stakeholders (the caregivers/families of the OVC) in the development of the NEP will enhance programme ownership and good will to support the continuation of the programme even after the study.Training the caregivers/families of the OVC using the educational materials and involving them in the delivery thereof will empower them to continue with the programme even after the study.

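### The children's dietary diversity score is obtained through the caregivers whom the programme trains, so over-reporting after training could appear as a dietary effect

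*Protocol article*

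**What the plan says.** **Who reports.** In the Protocol article, section Food intakes using 24-h recall: "A single day non-quantified 24-h recall of OVC will be obtained from the participants via their caregivers/families". Foods are sorted into nine groups. Each group scores one if any item from it was eaten and zero otherwise, and the sum is the IDDS.

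**What the score is for.** The same section relies on it as a measure of change: "The IDDS is sensitive to assessing the change in diet before and after an intervention to detect any improvement". Data management and analysis compares the outcomes other than QoL across baseline, week 12 and week 24, with baseline values as covariates.

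**Who is taught.** Three sections name the caregivers:
- Intervention: the programme will "provide guidance on how to overcome the barriers to healthy eating to enable the caregivers of the intervention group to adopt typical behaviors". Dietary diversity is one of its listed targets.
- Food intakes using photovoice: needs found there will be "incorporated into the NEP that will be developed and implemented to capacitate the caregivers/families of OVC".
- Sustainability aspects of this study: "Training the caregivers/families of the OVC using the educational materials".

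**Who is measured.** Recruitment and retention of participants: "We estimated that a total of 520 students aged (12–17 years) will be selected". They come from secondary schools.

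**The concern.** The person who has been taught which foods a child should eat is also the channel through which the child's intake is reported. Someone who has attended a 12-week programme knows that they attended it. If such caregivers tend to name foods they have learned are desirable, the tendency starts after baseline and is tied to the intervention arm. It is then a differential error, which shifts the between-arm difference and does not merely add noise.

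The score is easy to move. The recall is non-quantified and covers one day, and any item from a group earns the full point. One extra food named from a group not otherwise reported adds one point on a scale of zero to nine.

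A second weakness concerns coverage. A caregiver cannot directly observe what a secondary-school pupil eats at school.

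At stake is the interpretation of the dietary result. A significant IDDS difference could reflect a change in diet, a change in reporting, or both, and the data as planned could not separate them.

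**Working it through.** **1. Does the planned analysis protect against it?** Adjustment for baseline removes differences present before training. A reporting shift caused by training is absent at baseline and present at weeks 12 and 24, so the adjusted comparison still contains it.

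**2. Is there an independent check?** The only other record of the children's food is photovoice. The caregivers/families take those pictures too. The material is qualitative, is used to open discussion, and is not described as a validation of the recall. The limitations in the Discussion do not mention reporting bias.

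**3. The plan's own figure.** The article computes a sample size only for QoL, with difference 5, SD 10, and Z values 0.84 and 1.96:

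n = 2 × 10² × (0.84 + 1.96)² ÷ 5² = 2 × 100 × 7.84 ÷ 25 = 62.72, rounded up to 63 per group.

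This reproduces the stated 63. Adding 100% gives the stated 126. Both are used below only as group sizes.

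**4. Illustration of size.** The article gives no SD for IDDS and no figure for over-reporting, so both are assumed:
- SD of 1.3 to 1.8 food groups.
- No true dietary effect.
- An excess over-report in the intervention arm, relative to control, of b = 0.3 of a group. This corresponds to 3 in 10 caregivers naming one extra group.
- Independent observations and a two-sided 5% test.

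SE = SD × √(2/n); δ = b ÷ SE; false-positive rate = P(Z > 1.96 − δ) + P(Z < −1.96 − δ).

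| SD | n per group | SE | δ | False-positive rate |
|---|---|---|---|---|
| 1.3 | 63 | 0.2316 | 1.295 | 0.2531 + 0.0006 = 25% |
| 1.8 | 63 | 0.3207 | 0.935 | 0.1528 + 0.0019 = 15% |
| 1.3 | 126 | 0.1638 | 1.832 | 0.4489 + 0.0001 = 45% |
| 1.8 | 126 | 0.2268 | 1.323 | 0.2620 + 0.0005 = 26% |

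**5. Sensitivity to the assumptions.** With b = 0.5 the same formula gives 34–58% at 63 per group and 60–86% at 126. With b = 0.25 and SD of 1.0, 1.5 and 2.0 it gives 29%, 15% and 11% at 63, and 51%, 26% and 17% at 126. The rate rises with n because the bias stays fixed while the standard error shrinks.

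**The case against.** **The wording is loose.** The recall comes from the participants by way of their caregivers, and the section then speaks of the participants' recall being complete. The recruited participants are the students, so the caregiver might be a means of access or a joint informant. This stands in part. Some input from the child is possible, but the caregiver is still the stated channel, and no recall taken from the child alone is described. A reader might infer that the child is never asked. The text does not settle that.

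**Control caregivers may feel some pressure too.** A reader might infer that only trained caregivers have reason to over-report. The article does not say what control caregivers receive. The photo discussions on healthy food and the caregiver questionnaire listing the nine food groups are not confined to one arm. What matters is the excess in the intervention arm. It is plausible, but not established.

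**The error rates follow from assumed inputs.** This stands. Any fixed bias set against a small standard error inflates the rate. The figures show what would follow from a given bias. They are not evidence that it exists or of how large it is.

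**A change of respondent may move the bias.** The article describes a programme for the children that integrates caregivers, and gives intervention participants a workbook and a leaflet. Adolescents who see these, or live with trained caregivers, may also over-report. This stands, and limits what the fix can claim.

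**The reach is limited.** This stands as well. IDDS is one of several secondary outcomes. Caregiver nutrition knowledge, attitude and practices lie closer to the teaching than IDDS does. A reader might infer that the QoL result, or a planned diet-to-QoL pathway, is undermined. But QoL comes from a questionnaire for children and adolescents, and the article lists QoL and dietary diversity side by side as targets without planning a mediation analysis.

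**Conclusion.** The point holds as a risk to one secondary outcome. The article fixes the caregiver as the channel for the recall and makes caregivers the trained group. Over-reporting after training would be differential, baseline adjustment would not remove it, and the caregiver-taken photographs are no independent check. Because the respondent is a data-collection choice, an analysis plan could not repair it afterwards.

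The size is unknown. The illustrative rise from 5% to about 15–25% at 63 per group, or 26–45% at 126, depends on an assumed SD of 1.3 to 1.8, an assumed net over-report of 0.3 of a group, no true effect and independent observations. It should not be quoted as an estimate of the trial's actual error rate.

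The primary QoL outcome, accelerometry, body composition and school records do not depend on the caregiver's recall. The change is worth making because it is cheap and diet is a named target of the programme.

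**What to change.** Before baseline, so that all time points match:

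- State that the adolescent is the respondent for the 24-h recall at baseline, week 12 and week 24, interviewed by the research assistants whom Data procedures already has trained in dietary assessment.
- Keep the caregiver only as a supplement on ingredients of home-cooked dishes.
- Balance recall weekdays between arms. The article already spreads recalls over all days of the week but does not say they are balanced by arm.
- Report IDDS as an unblinded self-report outcome, with possible differential reporting stated as a limitation.

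**Cost.** This changes the respondent in an interview already planned. The children are already seen in person for anthropometry, but the article does not say where or when the recall is taken, so some rescheduling may be needed.

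**Downsides.** Adolescents may know less about what goes into mixed dishes. If exposed to the programme materials they may over-report as well. The change takes the directly trained reporter out of the main role and covers food eaten at school, so it reduces the bias but does not remove it.

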#### (b) Body composition and Anthropometric measurements

Tanita Dc-430 Body Composition Analyser (BCA) will be used to measure participants weight and body composition. Participants will be allowed to stand on the BCA without shoes or socks. Participants’ age, gender, and height will be entered into the BCA for calculations. The equations proposed by Clasey et al., for estimating the body composition of young children will be used to calculate the percentage of OVC’s body fat [33].

Weight and height of the OVC will be measured using standard techniques. Weight will be captured when an OVC stands on the BCA. Height will be obtained by allowing the participants to stand barefooted with their feet and heels together, their buttocks and upper parts of the back touching the portable stadiometer. The researcher and the trained research assistants will ensure the participants’ shoulders are relaxed with arms at the sides. While the participants will be instructed to take and hold a deep breath as the head is expected to be in straight position. The researcher will position the headboard of the device (portable stadiometer) on the participant’s head. Participants’ Body mass index (BMI) will be calculated as the ratio between the weight (kg) and height (m^2^).

The BMI of the OVC will be used to measure the occurrence of central lipohypertrophy and peripheral lipoatrophy which are significant problems among HIV-infected population. It will also be used to determine the risk of malnutrition (overweight and underweight) among the OVC.

The methods described by the American College of Sports Medicine [34] will be used to measure the Triceps and skin folds of the OVC.

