### Sample size

The sample size in this study was estimated based on the expected number of consenting participants in the two groups (control and the intervention group). This study desired 80% power (Z_β_ = 0.84) to estimate sample size with confidence interval (Z_∝/2_ = 1.96) of 95% as used in previous studies [16]. The investigator desires to detect a difference (d) of 5 points on a 100 point scale of QoL constructs between pre and post intervention [16, 17]. Standard deviation (*σ*) of 10 is expected in the QoL constructs between pre and post intervention [17]. Sample size (n) of 63 OVC per group (control and the intervention) to make a total of 126 OVC using the formular below is projected [18, 19].

*n* = 2(*σ*)2(*Z*_*β*_ + *Z∝*/2)2 ÷ *d*2

In order to compensate for non-response and drop out, 100% will be added to make a sample size of 126 anticipated consenting participants per group to make a total of 252 participants [18]. For the need’s assessment (Phase 1) a total of 252 is appropriate but 520 is proposed in order to further compensate for non-response and drop out.

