### Secondary outcomes

The following data will be collected to assess secondary outcomes.

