### Data management and analysis

The quantitative data will be entered into EXCEL (version 15; 2016), and data will be cross-checked by re-entering the data on a separate spreadsheet for comparison. Double data entry will be done to ensure the quality of the data. Data will be analyed using the Release 10, 2007 of Stata Statistical Software and SPSS packages. Data will be subjected to a normality test (Shapiro-Wilk test). The means, standard deviations (SD) and medians (interquartile range) of the continuous data will be calculated. The frequency and percentage distributions of categorical data will be described. The reliability test (Cronbach alpha) will be done to measure the internal consistency of the questionnaires.

The nutrition knowledge scores of participants will be calculated based on a possible maximum of 60. Each subsection ‘s score of the nutrition knowledge questionnaire will be calculated and converted to percentages. The mean percentage of knowledge scores will also be calculated. Whati et al., performance rating scale of < 34% - very poor; (ii) 34 to 51% - fair/below average; (iii) 52 to 57% - good/average; (iv) 58 to 75% - very good/above average; and (v) 76 and above – excellent [45, 55] will be used to classify the nutrition knowledge performance.

Nutrition attitudes have eight dichotomous (agree, disagree) responses questions and the score will be the percentage of the total possible score (affirmative responses) using 60% as the cut-off for poor attitude performance [44].

The dietary practices will be classified based on how often participants consumed the FAO nine food groups [31] in the previous week. Participant’s lifestyle will also be classified based on the number of drinks containing alcohol and cigarettes consumption per day.

The construct of the QoL, nutrition knowledge and IDDS will be summarised by sex and age using percentages and 95% confidence intervals. Analysis of variance will be used to compare the intervention and control groups, to confirm the similarity in participant populations.

Multivariate regression analysis will be used for group comparison of overall QoL and the QoL constructs of the intervention and control groups. Other measurable outcomes will be compared (the baseline, week 12 and week 24) using baseline data as covariates. All the testing will be done at the 0.05 level of significance.

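### Percent body fat is assigned to equations that the protocol itself labels as meant for young children, although every participant is a secondary-school pupil aged 12–17

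*Protocol article*

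**What the plan says.** Body composition is one of the secondary outcomes of the protocol article. Section (b) Body composition and Anthropometric measurements has participants stand on a body composition analyser and says that "Participants’ age, gender, and height will be entered into the BCA for calculations". The next sentence turns to percent body fat and gives it to published equations "for estimating the body composition of young children will be used to calculate the percentage of" the participants' body fat.

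The population is set in two other places. Recruitment and retention of participants states: "We estimated that a total of 520 students aged (12–17 years) will be selected". It adds: "Participants will be chosen from secondary schools in Soweto". Eligibility criteria repeats the 12–17 age limit and provides for no younger group.

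The article gives no age range, derivation sample or validation sample for the equations, and does not say that they have been checked in adolescents.

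**The concern.** This is a stated choice of calculation, described in terms that exclude the whole planned sample. It is therefore more than a detail that a condensed article has left to a fuller document.

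A prediction equation is only as good as its fit to the people it is used on. If its error changes with age or sex, a sample of both sexes spread over 12–17 years will carry different errors in different pupils. Three uses of the outcome could then be affected:

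- the description of body composition in the Phase 1 needs assessment;
- the Phase 1 associations of body composition with quality of life, dietary diversity, physical activity and academic performance (first objective, end of Background), which feed the content of the education programme;
- the Phase 3 comparison, where groups are quasi-experimental and recruited by convenience, so that balance in age and sex is not assured.

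The text also leaves the source of the outcome uncertain. The analyser is said to measure body composition, with inputs entered for its own calculations, yet percent fat is then assigned to outside equations.

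**Working it through.** **Passages side by side.** No formula decides the main point; it is a comparison of wording.

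| Item | Protocol article | Section |
|---|---|---|
| Population named for the equations | young children, no numeric limits | (b) Body composition and Anthropometric measurements |
| Eligible ages | 12–17 years | Eligibility criteria |
| Source of participants | secondary schools | Recruitment and retention of participants |
| Extension or validation of the equations for adolescents | none stated | – |

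On ordinary meaning, a secondary-school pupil of 12 or older is not a young child. By the protocol's own words, all participants lie outside the named population.

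**The plan's own design figure.** The sample size is driven by quality of life: "The investigator desires to detect a difference (d) of 5 points on a 100 point scale of QoL constructs". With SD 10, the stated formula gives 2 × 10² × (0.84 + 1.96)² ÷ 5² = 62.72, rounded up to 63 per group, as the article says. Percent fat plays no part in it.

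**Illustration of where an error would matter.** The documents give no error size. Assume, for illustration only, an error that is linear in age at k = 0.5 to 1.0 percentage points of fat per year.

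1. Between pupils aged 12 and 17 (5 years): 5 × 0.5 = 2.5 to 5 × 1.0 = 5 points. This enters Phase 1 levels and associations in full, because there is no earlier value to absorb it.
2. Between two groups whose mean ages differ by 1 year (also assumed), unadjusted means at one visit: 1 × 0.5 = 0.5 to 1 × 1.0 = 1.0 point.
3. Within a pupil over 24 weeks (24 ÷ 52 = 0.46 year): 0.46 × 0.5 = 0.23 to 0.46 × 1.0 = 0.46 point. Under a linear error this shift is the same in both groups, so the difference in mean change between groups carries no bias.
4. With baseline as a covariate, as Data management and analysis plans: the spurious group difference is k × 1 year at both baseline and follow-up. The adjusted difference is therefore (1 − b) × k × 1 year, where b is the slope of follow-up on baseline. It goes from the full 0.5–1.0 point at b = 0 to zero at b = 1. For a measure that tracks closely within a child, b is near 1 and little remains.

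The consequences are therefore mainly cross-sectional.

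**The case against.** The strongest reply is that the label may be loose wording. The protocol calls its own participants children throughout, and the derivation ages stand in a cited paper that is not at hand. The equations may well cover 12–17. This stands as a limit on the claim. It does not rescue the sentence, because either the equations do not suit the sample or their description is wrong, and each calls for an edit.

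A reader might go further in four ways that the documents do not support:

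- **That the equations were fitted before puberty and are invalid in adolescents.** No derivation ages or pubertal stages are given. The article names a population, not a numeric range.
- **That the analyser's own output is the better of two methods.** Its age coverage is not stated either. The section can also be read as one sequence, in which the analyser measures and the equations convert.
- **That the error passes into the intervention effect.** Baseline adjustment and a drift common to both groups would remove most of it, as the working shows. A residue could remain if the error were not linear in age or if the groups matured differently, but its size cannot be derived.
- **That the points-per-year figures measure the bias.** They are assumptions. Neither size nor direction follows from the documents.

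It is also fair to say that percent fat is one component of one of five secondary domains, and that the protocol assigns malnutrition risk to body mass index. That bears on severity, and it is accepted.

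**Conclusion.** The point holds as a conflict between the equations' stated population and the trial's own population. All participants are outside the group the protocol names for the calculation, and nothing in the article bridges the gap. This rests only on the protocol's wording and on reading young children in its ordinary sense.

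The consequence cannot be quantified from the documents. If the error varies with age or sex, it would chiefly distort Phase 1 levels and cross-sectional associations, and much less the baseline-adjusted Phase 3 comparison. The primary quality-of-life outcome and the sample size are unaffected. Severity is minor: one secondary outcome.

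**What to change.** In section (b) Body composition and Anthropometric measurements:

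1. Check the derivation and validation ages of the cited equations. If they cover both sexes aged 12–17, keep them and correct the description.
2. If they do not, replace them with an equation whose derivation or validation sample covers both sexes aged 12–17 and whose inputs are among the measurements already planned. The analyser's own percent-fat output may serve only if its coverage of these ages is confirmed.
3. State that this single calculation defines percent body fat at baseline, week 12 and week 24.

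The cost is a sentence or two of text and a check of the source. No new measurement is needed provided the chosen equation uses planned inputs; since the article does not list the inputs of the present equations, this should be confirmed when choosing. The downside of replacement is less direct comparability with studies that used the young-children equations. The choice should be settled before baseline data are analysed, so that the outcome definition does not change during the study.

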### Data procedures

Before the needs’ assessment data collection, a series of training sessions will be held to train the research assistant responsible for taking measurements, including QoL, dietary intake assessments, body composition, and anthropometric measurements, physical activities and nutrition KAP of the caregivers. The training will be for three weeks, to be held at the South African Research Chair: Education and Care in Childhood, Faculty of Education University of Johannesburg project office. To ensure standardisation and quality of data collection, this training will include an overview of all the measurement procedures in the protocol, and demonstration of the measurement techniques. The questionnaires will be subjected to face validity, such as clarity, simplicity, and readability of the content of the questions. This process will be conducted by the principal investigators [52, 53]. The questionnaires will be pretested following the procedure described above among at least 50 conveniently sampled OVC and ten caregivers. The reliability test will be done (using Cronbach alpha) to measure the internal consistency of the questionnaires. Anthropometric data will be collected individually using the school clinic. The dial indicator of the BCA will be checked regularly and adjusted to the appropriate zero reading position before use. A non-stretchable tape measure will be used in measuring the MUAC. To ensure reliability, measurements will be done two times for each participant [54].

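### BMI is named as the measure of central lipohypertrophy and peripheral lipoatrophy, but weight over height squared cannot show where fat lies

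*Protocol article*

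**What the plan says.** The relevant text is in the protocol article, under Secondary outcomes, (b) Body composition and Anthropometric measurements. BMI "will be calculated as the ratio between the weight (kg) and height" in square metres. Its first stated use is: "The BMI of the OVC will be used to measure the occurrence of central lipohypertrophy and peripheral lipoatrophy". The reason given is that these are important problems in people with HIV infection. A second use follows: "It will also be used to determine the risk of malnutrition (overweight and underweight) among the OVC".

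Other body measures are planned. Published equations "will be used to calculate the percentage of OVC’s body fat". A cited sports-medicine method "will be used to measure the Triceps and skin folds of the OVC". Under Data procedures, the article adds: "A non-stretchable tape measure will be used in measuring the MUAC". None of these measures is linked to lipohypertrophy or lipoatrophy; BMI alone is given that task. The article names no waist or other trunk measurement, and no skinfold site besides the triceps.

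**The concern.** Central lipohypertrophy is a gain of fat on the trunk, and peripheral lipoatrophy is a loss of fat from the limbs. Detecting either requires a measurement that separates body regions. The article assigns the task to an index that adds all regions together before dividing by height squared. When the two conditions occur together they push body weight in opposite directions, so the index may not move at all.

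What is at stake is any statement of how often these conditions occur among the participants. Such a figure would not describe fat distribution. It could also travel further than the final report: under Planning and development of the nutrition education programme, the Phase 1 results are to guide the programme's content, so an invalid prevalence could be read as an identified need.

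**Working it through.** The plan gives no figure to reproduce here. The check applies the article's own BMI definition to shifts of fat between regions.

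**Inputs**
- BMI definition, from section (b): BMI = weight (kg) / height (m)².
- Illustrative adolescent, assumed and not from the documents: 50 kg, 1.60 m, so height squared is 2.56 m².
- Regional changes, assumed: 1 to 4 kg at the trunk, the limbs or both.

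**Formula**
Write weight as trunk + limbs + rest. Then BMI = (trunk + limbs + rest) / height². A change of *a* kg at the trunk and *b* kg at the limbs alters BMI by (*a* + *b*) / height². Only the sum *a* + *b* enters.

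**Results**

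| Trunk change (kg) | Limb change (kg) | Weight (kg) | BMI (kg/m²) |
|---|---|---|---|
| 0 | 0 | 50 | 50 / 2.56 = 19.53 |
| +2 | −2 | 50 | 19.53 |
| +4 | −4 | 50 | 19.53 |
| −2 | +2 | 50 | 19.53 |
| +2 | −1 | 51 | 51 / 2.56 = 19.92 |
| +2 | 0 | 52 | 52 / 2.56 = 20.31 |
| 0 | −2 | 48 | 48 / 2.56 = 18.75 |

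A second assumed starting point behaves in the same way. At 45 kg and 1.55 m, BMI is 45 / 2.4025 = 18.7, and it is still 18.7 after 1 kg moves from limbs to trunk.

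**Reading**
1. Rows 2 and 3 show both conditions present together, moderately and then more strongly, with BMI unchanged.
2. Row 4 is the opposite pattern, and its BMI is the same as in rows 1 to 3. One BMI value is therefore compatible with no redistribution, with redistribution, and with its reverse.
3. In rows 5 to 7 BMI moves, but exactly as it would for a 1 kg or 2 kg weight change spread over the whole body. A rise does not indicate trunk fat, and a fall does not indicate limb loss.
4. Hence no BMI cut-off separates participants with either condition from those without it.

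**Do the other planned measures repair the statement?** The percentage of body fat, as described, is a whole-body figure and does not locate fat. The triceps skinfold is a regional measure of subcutaneous fat at a limb site and bears on the peripheral condition, but the article does not assign it to that use. MUAC is the circumference of the whole arm, muscle and bone included, so it is not a pure fat measure. Nothing named measures the trunk. The statement about BMI therefore stands uncorrected elsewhere in the article.

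**The case against.** The strongest reply is that the sentence is incidental. Fat redistribution is not among the stated objectives, the sample size or the analysis described under Data management and analysis, and no hypothesis rests on it. The worked example is also close to a tautology: unchanged weight and height must give unchanged BMI. Both remarks are fair, and they limit the importance of the point. They do not rescue the sentence, because the tautology is the reason the measure fails. Nor is this a detail that a condensed article leaves to a fuller document: the article positively names BMI as the measure, and a fuller protocol could replace that rule but could not make it valid.

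A reader might go further and infer that under- and overweight will be classified from raw BMI with fixed cut-offs, ignoring age and sex in growing 12–17-year-olds. The article does not say this. It names neither a reference nor a cut-off, and the choice of growth reference may be left to the full protocol or analysis plan. A reader might likewise infer that growth will be mistaken for an intervention effect in the comparison of non-randomised groups. That is not established either. Data management and analysis plans to use baseline data as covariates and to check that the groups are similar, growth common to both groups cancels in a concurrent comparison, and BMI is not named there as an analysed endpoint.

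Finally, HIV status is absent from the listed eligibility criteria and described measures, although HIV infection is the stated reason for interest in these conditions. An article need not list every recorded variable, so nothing here depends on that absence.

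**Conclusion.** The point holds for one statement: BMI, as the article defines it, cannot measure the occurrence of central lipohypertrophy or peripheral lipoatrophy. The failure is complete rather than a loss of precision, since shifts of 2 kg or 4 kg between limbs and trunk, in the direction of the conditions, and of 2 kg in the opposite direction, all leave BMI at 19.53 in the example. The body sizes and shifts are assumed, but the conclusion does not depend on them, because it follows from the formula for any weight and height. Any occurrence reported this way would be invalid.

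The reach is limited. The affected item is a secondary, descriptive measure; the quality-of-life primary outcome and the sample size of 63 per group before inflation are untouched. The use of BMI for overweight and underweight is not shown to be wrong, and the most that can be asked there is a clarification.

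**What to change.** Delete the use of BMI for lipohypertrophy and lipoatrophy, and make no claim about the occurrence of either condition from it. If fat distribution is still of interest, describe peripheral subcutaneous fat from the triceps skinfold already planned, with MUAC reported only as a supporting measure of arm size. Make no statement on central fat unless a trunk measure is in the data set; if other skinfold sites are in fact taken, name them.

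As a separate clarification, name the age- and sex-specific BMI reference and the cut-offs that will define overweight and underweight.

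The cost is a change of wording. Age, sex, weight, height, triceps skinfold and MUAC are already to be recorded, so no new data collection is needed. A central-fat claim would cost more only if no trunk measure is currently taken and the investigators choose to add one.
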